## **6.1 Study Product**

### **6.1.1 Formulation, Packaging, and Labelling**

Each vial of the study medication contains an extractable volume of at least 1 ml

- solution for subcutaneous injection or
- concentrate for solution for infusion.

|                                |                             |                      |
|--------------------------------|-----------------------------|----------------------|
| Protocol Amendment 7.1         | Study no.: NM-V-101         | Page 36 of 85 |
| Date of Amendment: 15 Feb 2018 | EudraCT No.: 2012-000066-37 |                      |

The clear, colorless aqueous solution contains 70 IU / ml Ancrod-Fibrinogenase or placebo (see point 6.2). It will be distributed as clear 2-mL glass vials, closed with a rubber stopper, which in turn is covered with a red flip cap.

**Table 1: Active Formulation**

| Ingredient | Unit/weight                            |
|-------------------|-----------------------------------------------|
| Active substance  | 70 IU/mL ancrod-fibrinogenase (63 – 77 IU/mL) |
| Buffer            | 10 mM sodium phosphates, 0.9% sodium chloride |
| pH                | 6.5 – 7.1                                     |

One treatment kit contains 2 cardboard boxes. One cardboard box contains 6 clear glass vials, the second cardboard box contains 3 clear glass vials.

- 1 of these 9 vials is intended to be used for intravenous administration on Day 1 as described under point 6.1.2.
- 6 of these 9 vials are intended to be used for subcutaneous administration on Day 2, 4 and 6, corresponding to 2 vials for each of these treatment days, as described under point 6.1.2.
- 2 of these 9 vials are intended for backup reasons.

The vials and the treatment kits are labeled in compliance with legal and regulatory requirements of the respective country.

## **6.1.2 Preparation, Administration, Storage, and Dosage of Study Product**

### **Administration on Day 1**

The solution prepared for intravenous administration on Day 1 will contain a concentration of 1.4 IU/ml of ancrod-fibrinogenase or placebo. Therefore 1,0 mL concentrate for solution for infusion (containing 70 IU/mL ancrod-fibrinogenase or placebo) is to be taken out of one vial by a 1 ml syringe and transferred through a three-way-stopcock into a 50 mL perfusor syringe which will subsequently be filled with saline to achieve a final volume of 50 ml.

Solutions for infusions shall be freshly prepared and must be administered within one hour after preparation.

The infusion on Day 1 is to be administered at a rate of 0.167 IU/kg/hr for a maximum of 3 hours. A single 50-mL syringe will thus be sufficient for a patient weighing up to 140 kg.

The individual infusion rate is calculated according to the formula:

|                                |                             |                      |
|--------------------------------|-----------------------------|----------------------|
| Protocol Amendment 7.1         | Study no.: NM-V-101         | Page 37 of 85 |
| Date of Amendment: 15 Feb 2018 | EudraCT No.: 2012-000066-37 |                      |

$$\text{Infusion Rate} = \frac{\text{Dose} \times \text{Body Weight}}{\text{Concentration}}$$

with the following dimensions:

|                       |                |
|-----------------------|----------------|
| Infusion rate: | ml/h    |
| Dose:          | IU/kg/h |
| Body weight:   | kg      |
| Concentration: | IU/ml   |

Example for a 75 kg patient:

$$\text{Infusion Rate} = \frac{0.167 \times 75}{1.4} = 8.95 \text{ ml/h}$$

Since the ancrod dose and concentration of the infusion solution are fixed in this study, the formula can be simplified as follows:

$$\text{Infusion Rate (ml/h)} = 0.1193 \times \text{Body weight (kg)}$$

The calculated infusion rate has to be documented in the dosing worksheet (Appendix 17.4).

The maximum single dose applied intravenously is 70 IE.

It would apply for a 140 kg patient having a screening fibrinogen concentration of > 360 mg/dL and receiving a 3-hour infusion of 0.167 IU/kg/h ancrod-fibrinogenase.

### **Administration on Days 2, 4, and 6**

For the subcutaneous injections on Days 2, 4, and 6 the concentrate solution containing 70 IU/mL ancrod-fibrinogenase or placebo will be used. The contents of one or two vials will be drawn into a 2 ml syringe, the volume adjusted according to the patient's weight. Injections shall be freshly prepared and must be administered within one hour after preparation.

The volume to be administered is calculated as follows:

$$\text{Injection volume (ml)} = 0.0143 \times \text{Body weight (kg)}$$

The calculated injection volume has to be documented in the dosing worksheet (Appendix 17.4).

The maximum single dose applied subcutaneously is 140 IE.

It would apply for a patient on treatment day 2, and optionally on day 4 and day 6.

### **Storage**

|                                |                             |                      |
|--------------------------------|-----------------------------|----------------------|
| Protocol Amendment 7.1         | Study no.: NM-V-101         | Page 38 of 85 |
| Date of Amendment: 15 Feb 2018 | EudraCT No.: 2012-000066-37 |                      |

The treatment kits must be stored refrigerated at + 2 °C to + 8 °C. After vial opening the vial the solution should be used immediately either as a concentrate for solution for infusion or as a solution for s. c. injection.

## 6.2 Reference Product

**Table 2: Placebo formulation**

| Ingredient       | Unit/weight                                    |
|------------------|------------------------------------------------|
| Buffer (aqueous) | 10 mM sodium phosphates, 0.9 % sodium chloride |
| pH               | 6.5 – 7.1                                      |

## 6.3 Concomitant Medication

Paracetamol may be taken for pain relief.

## 6.4 Precautionary and Prohibited Medications and Procedures

### 6.4.1 Prohibited Medications and Procedures

Subjects who received thrombolytic agents (e.g. rt-PA, urokinase, streptokinase), anticoagulants (e.g. warfarin, phenprocoumon, heparin, low molecular weight heparin, factor Xa inhibitors such as rivaroxaban, apixaban, dabigatranetexilat), antiplatelet drugs (e.g. pentoxifylline, naftidrofuryl, prostacyclin, prostaglandin, nicotinic acid, acetylsalicylic acid, abciximab) within 72 hours or systemic available corticosteroids (tablets, capsules, injections or infusions) within 30 days prior to screening are not to be enrolled in the study. A previously existing topic corticosteroid therapy with ointments, inhalativa or nasal sprays can be discontinued, reduced or continued in a stable dose during the treatment phase.

Thrombolytic agents should not be given within 5 days after initiating study drug. Anticoagulants should not be given within 72 hours after initiating study drug infusion.

In addition, the following procedures and medications are not allowed throughout the study with the exception of the rescue medication (see section 6.5):

- Hyperbaric oxygen
- Plasmapheresis
- Anticoagulants (e.g. warfarin, phenprocoumon, heparin, low molecular weight heparin, factor Xa inhibitors such as rivaroxaban, apixaban, dabigatranetexilat)
- Antiplatelet drugs (e.g. pentoxifylline, naftidrofuryl, prostacyclin, prostaglandin, nicotinic acid, acetylsalicylic acid)

|                                |                             |                      |
|--------------------------------|-----------------------------|----------------------|
| Protocol Amendment 7.1         | Study no.: NM-V-101         | Page 39 of 85 |
| Date of Amendment: 15 Feb 2018 | EudraCT No.: 2012-000066-37 |                      |

- Thrombolytic agents (e.g. rt-PA, urokinase, streptokinase)
- Hydroxyethyl starch (HAES), low-molecular-weight dextran, local anesthetics (lidocain, procain)
- Blood or blood products
- Systemic available corticosteroids and start of therapy with topic corticosteroids
- NSAIDs

#### **6.4.2 Precautionary Medications and Procedures**

Ancrod should not be used in patients receiving drugs that block the reticuloendothelial system (e.g., dextran) or interfere with the fibrinolytic system such as  $\epsilon$ -aminocaproic acid or tranexamic acid.

#### **6.4.3 Prophylactic Medications and Procedures**

Not applicable.

### **6.5 Rescue Medications**

Corticosteroids, vasodilators, vitamin C, vitamin B12 or antihistamines are allowed if deemed necessary at the discretion of the investigator, if, on day 8, no improvement or worsening of symptoms has been observed.

### **6.6 Randomization and Blinding Procedures**

The present study is carried out in a double-blind, placebo-controlled study design, i.e. neither patient nor investigator have been informed whether the test substance or a placebo have been administered. The randomization is done in a 2:1 ratio verum to placebo.

The randomization was carried out by Medizinisches Wirtschaftsinstitut GmbH (MWI), München, using commercial software (RANCODE Professional, Version 3.6). A randomization list was generated in ascending order with the block randomization method in the above-mentioned ratio between verum and placebo. Further characteristics of the block randomization carried out are not mentioned until being cited in the Biometric Report or the Clinical Study Report at the end of the study once it has been unblinded. The randomization list is kept by MWI.

All investigators have to follow and ensure the trial's randomization procedure. To this end, each center has to treat the patients meeting the inclusion criteria with the investigational products provided in ascending order, taking care of the chronological order of the patients' inclusion. The

|                                |                             |                      |
|--------------------------------|-----------------------------|----------------------|
| Protocol Amendment 7.1         | Study no.: NM-V-101         | Page 40 of 85 |
| Date of Amendment: 15 Feb 2018 | EudraCT No.: 2012-000066-37 |                      |

first patient included in a study center receives the investigational product with the lowest number given to the center. The second patient in a center receives the product one number higher.

The inclusion has to be exactly documented stating the precise date and time. Furthermore, the investigators have to document immediately every premature unblinding of a patient (e.g. unblinding because of a SUSAR or accidental unblinding) including prompt information of the monitor and stating the reasons to the Sponsor.

#### **6.6.1 Maintenance of Study Treatment Randomization Codes**

MWI prepares emergency envelopes corresponding to the labeled test substances, so that an individual unblinding will be possible if needed. The numbered emergency envelopes have to be dispatched together with the identically numbered test substances.

The randomization list and the allocation to treatment groups will not be known to the investigator, sponsor, or any other person involved in the conduct of the study except staff involved in IMP (Investigational Medicinal Product) production, until completion of the study, except in the case of an emergency. Each investigator will be provided with emergency code break envelopes containing the information to which treatment an individual patient number was allocated. This information will only be eligible after opening the envelope. An envelope may only be opened in the case of emergency when it is necessary for medical reasons to know which study treatment a specific patient has received. The investigator has to document the reason for breaking the code. The signed and dated letter will be archived in the investigator's file.

Furthermore, the drug safety officer of the sponsor will be provided with emergency code break envelopes containing the information to which treatment an individual patient number was allocated. This information will only be eligible after opening the envelope. An envelope may only be opened in the case of a suspected unexpected serious adverse reaction (SUSAR) to fulfill the reporting obligations to the authorities and ethics committee according to chapter 7.11 of European Commissions guidance (CT-3). The drug safety officer will not inform other sponsor's staff or investigator about the unblinded information unless unblinded information is judged necessary for safety reasons. The drug safety officer has to document the reason for breaking the code. The signed and dated letter will be archived in a closed safe until the study is completed.

The entire study is not unblinded until its completion with closure of the data base. Upon completion of the study, all distributed emergency envelopes will be collected by the monitor, each envelope being examined for having been opened.

|                                |                             |                      |
|--------------------------------|-----------------------------|----------------------|
| Protocol Amendment 7.1         | Study no.: NM-V-101         | Page 41 of 85 |
| Date of Amendment: 15 Feb 2018 | EudraCT No.: 2012-000066-37 |                      |

## 6.6.2 Additional Measures to Minimize/Avoid Bias

Not applicable

## 6.7 Drug Accountability

The investigator will record and acknowledge receipt of all shipments of study drug. The study drug must be kept in a locked area with restricted access, stored and handled in accordance with the manufacturer's instructions. The investigator is responsible for maintaining documentation showing the amount of study drug provided to the investigational site and dispensed to each study patients (see Appendix 17.4). Discrepancies in study drug accountability must be explained and documented. An inventory of study drugs will be maintained. The monitor is responsible for verifying the investigator's documentation on receipt, use and return of study drug. The monitor will prepare a final report of the accountability of the study drug for filing in the investigator's file. Unused medication will be returned to the sponsor for destruction.

## 7 Therapy

### 7.1 Treatment Schedule

Patients will receive study medication on Days 1, 2, 4, and 6 of the study as follows:

#### Administration and Dosage on Day 1

On Day 1 (Visit 1) study medication will be administered as intravenous infusion. The duration of the infusion will be adjusted according to the screening fibrinogen concentration as assessed prior to the infusion in the local laboratory:

- 2-hour infusion of 0.167 IU/kg/h ancrod-fibrinogenase or placebo at a screening fibrinogen concentration of  $\geq 180$  to  $\leq 360$  mg/dL, corresponding to a total dose of 0.33 IU/kg.
- 3-hour infusion of 0.167 IU/kg/h ancrod-fibrinogenase or placebo at a screening fibrinogen concentration of  $> 360$  mg/dL, corresponding to a total dose of 0.50 IU/kg.

The maximum single dose applied intravenously is 70 IE.

It would apply for a 140 kg patient having a screening fibrinogen concentration of  $> 360$  mg/dL and receiving a 3-hour infusion of 0.167 IU/kg/h ancrod-fibrinogenase.

Study drug will be administered through a dedicated intravenous line using an infusion pump.

Patients with a baseline fibrinogen level of  $<180$  mg/dL must not receive the study drug.

|                                |                             |                      |
|--------------------------------|-----------------------------|----------------------|
| Protocol Amendment 7.1         | Study no.: NM-V-101         | Page 42 of 85 |
| Date of Amendment: 15 Feb 2018 | EudraCT No.: 2012-000066-37 |                      |

If the infusion has been interrupted for any reason (e.g., infiltration), it should be resumed at the same infusion rate as before, i.e., the infusion rate may not be increased in an effort to administer the full dose within the original time frame.

Any deviation from the planned infusion duration has to be documented.

### **Administration and Dosage on Days 2, 4, and 6**

On Day 2, patients will receive a maintenance subcutaneous injection of investigational drug or placebo at a fixed dose of 1 IU/kg using undiluted solution. On Day 4 and Day 6 patients will receive maintenance subcutaneous injections only if the plasma fibrinogen concentration, measured on Day 2 is  $\geq 50$  mg/dl. If the fibrinogen concentration on Day 2 is lower than 50 mg/dl this patient may not receive further injections of ancrod.

The maximum single dose applied subcutaneously is 140 IE.

It would apply for a 140 kg patient on treatment day 2, and optionally on day 4 and day 6.

## **7.2 Compliance**

Not applicable.

## **7.3 Continuation of Therapy after the End of the Study**

If no improvement in efficacy measurements compared to the baseline value is achieved by the end of the double-blind treatment phase (Day 8; Visit 5), the patient will be allowed to be treated according to accepted Standard of Care.

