A variety of divergent treatment options have been employed in the treatment of SSHL, although most of them did not gain regulatory approval. Since in most cases the etiology of the condition cannot be determined, a causal therapy is not possible (Suckfüll, 2009). Currently, pentoxifylline, poly (O-2-hydroxyethyl) starch and naftidrofuryl are approved medicinal products for the treatment of sudden hearing loss within a wider indication for use. For all 3 products a comparison of Summary of Product Characteristics (SPCs) among European Union countries showed that the indication pertaining to sudden hearing loss only had been granted in Germany and Austria, whereas this indication was not listed in SPCs of other European countries. The conclusion reached in multiple publications and the current Consensus Guidelines of the German Society of Otorhinolaryngology - Head and Neck Surgery is that all current therapeutic approaches for the treatment of SSHL are considered empiric in nature, and that none of the currently used therapies has shown unequivocal efficacy. Based on a systematic review of randomized clinical studies it has further been concluded that no valid randomized clinical study exist to determine an effective treatment of SSHL (Conlin and Parnes, 2007a, 2007b). Furthermore, the authors stated that systemic steroids cannot be considered the gold standard of treatment, given the severe limitations

|                                |                             |                      |
|--------------------------------|-----------------------------|----------------------|
| Protocol Amendment 7.1         | Study no.: NM-V-101         | Page 20 of 85 |
| Date of Amendment: 15 Feb 2018 | EudraCT No.: 2012-000066-37 |                      |

of the landmark study of Wilson et al. (1980) suggesting their use. This statement is further supported by a review of the Cochrane Collaboration concluding that the value of steroids in the treatment of idiopathic SSHL remains unclear since the evidence obtained from randomized controlled studies is contradictory in outcome, in part because the studies are based upon a too small number of patients (Wei et al., 2006).

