## 2.4 Potential Risks and Benefits

### 2.4.1 Potential Risks

Due to its mode of action, bleeding may occur during ancrod treatment. The direct effect of ancrod on the coagulation cascade and on platelet function may cause microscopic hematuria, bleeding at puncture sites, bruising and, in rare cases, melena, epistaxis, and hematemesis (Latallo, 1983). Many bleeding adverse events are related to bruising and are of limited clinical significance. The

|                                |                             |                      |
|--------------------------------|-----------------------------|----------------------|
| Protocol Amendment 7.1         | Study no.: NM-V-101         | Page 23 of 85 |
| Date of Amendment: 15 Feb 2018 | EudraCT No.: 2012-000066-37 |                      |

bleeding risk appears to be increased when fibrinogen levels remained below 40 mg/dL for longer periods.

The relatively high incidence of adverse events observed in clinical studies in patients with acute ischemic stroke treated with ancrod may be attributed to advanced age, predisposition, and vulnerability of this patient population and cannot be extrapolated to patients with sudden hearing loss who will be treated with a different, moderate dosing regimen. Further, the incidence of adverse events observed in the direct comparison of defibrinogenation therapy with corticosteroid revealed no minor or major bleeding. Side effects were observed in 84.9% of patients who received defibrinogenation therapy and in 85.9% of patients who received corticosteroid treatment (Kubo et al., 1988).

Local reactions, such as urticaria and exanthema, are rare but may occur after subcutaneous use. Some patients who had received ancrod subcutaneously developed local irritation or itching. These skin reactions have responded to antihistamine therapy. There was no evidence of an allergic reaction in healthy subjects or in patients treated with ancrod repeatedly. Nevertheless, special attention should be paid to patients receiving a second course of ancrod because neutralizing antibodies may occur particularly after long-term subcutaneous administration.

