## 3.3. Study Conduct

Duration of trial:

- Per patient: Screening period of up to 36 hours, then 1-week double-blind treatment phase, then 12-week follow-up phase without study treatment
- First patient in (FPI): August 2013
- Last patient out (LPO): planned for September 2018.

The study is conducted in 24 sites in Germany and Czech Republic; whereas 8 sites enrolled actively patients.

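### Read literally, Protocol 7.3 opens unlisted standard care to non-improvers from Day 8, which conflicts with the study-long ban in 6.4.1 and is wider than the rescue list in 6.5

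*Combined protocol and SAP*

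**What the plan says.** Protocol 7.3 consists of one sentence. If the efficacy measurements show no improvement over baseline by Day 8 (Visit 5), "the patient will be allowed to be treated according to accepted Standard of Care". The heading speaks of therapy after the end of the study. The sentence names no drug and refers to neither 6.4.1 nor 6.5.

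Protocol 6.4.1 states that "the following procedures and medications are not allowed throughout the study with the exception of the rescue medication (see section 6.5". The list that follows includes hyperbaric oxygen, hydroxyethyl starch, systemic corticosteroids and antiplatelet drugs. The same section also uses the antiplatelet class as an enrolment exclusion: "antiplatelet drugs (e.g. pentoxifylline, naftidrofuryl, prostacyclin, prostaglandin, nicotinic acid, acetylsalicylic acid".

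Protocol 6.5 gives the only exception, for patients not improved or worse on Day 8: "Corticosteroids, vasodilators, vitamin C, vitamin B12 or antihistamines are allowed if deemed necessary at the discretion of the investigator". Protocol 2.4.1 and 3.1 and SAP 3.2 and 8.3 repeat these five classes.

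Protocol 2.1 reports that "pentoxifylline, poly (O-2-hydroxyethyl) starch and naftidrofuryl are approved medicinal products for the treatment of sudden hearing loss", within a wider indication, and that "the indication pertaining to sudden hearing loss only had been granted in Germany and Austria". On sites, SAP 3.3 says: "The study is conducted in 24 sites in Germany and Czech Republic".

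**The concern.** The same patient at the same visit falls under two rules. Section 6.5 gives a closed list. Section 7.3 gives an open permission, and the patient then stays in the study to Day 90. Three products that Protocol 2.1 describes as approved for this condition in Germany, a study country, are on the 6.4.1 list. A German investigator could therefore take 7.3 as permission to use them.

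What is at stake is mainly bleeding safety, and only for the drugs that 6.4.1 classes as antiplatelet. Protocol 2.4.1 says: "The direct effect of ancrod on the coagulation cascade and on platelet function may cause microscopic hematuria, bleeding at puncture sites, bruising". Adding an antiplatelet drug soon after the last dose is what the ban prevents. For hydroxyethyl starch and hyperbaric oxygen the point is the inconsistency alone.

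**Working it through.** The plan gives no figure for this point, so the check is a comparison of texts plus simple timing arithmetic.

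**1. The texts side by side**

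| Section | When | What is allowed or barred | Cross-reference |
|---|---|---|---|
| 7.3, heading | After the study | Continued therapy | none |
| 7.3, sentence | Day 8, no improvement | Accepted standard care, unlisted | none |
| 6.5 | Day 8, no improvement or worse | Five named classes | none |
| 6.4.1 | Throughout the study | Named drugs and procedures barred | exempts 6.5 only |

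The heading and the sentence of 7.3 disagree on timing. The sentence and 6.4.1 disagree on content. No text says which section takes precedence.

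**2. Last dose to Visit 5.** Protocol 4.2 allows the Day 6 dose on Day 6 or 7 and Visit 5 on Day 7, 8 or 9, never on the same day.
- Shortest gap: 7 − 6 = 1 day, or 8 − 7 = 1 day.
- Longest gap: 9 − 6 = 3 days.
- Patients stopped by the Day 2 fibrinogen rule: 7 − 2 = 5 to 9 − 2 = 7 days.

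**3. What the investigator knows at Visit 5.** Fibrinogen is measured at screening, Day 2 and Day 8 (SAP 9.2.4). The Day 2 sample is taken before all three 1 IU/kg injections, and the site learns only whether the value reached 50 mg/dL (Protocol 3.1). The Day 8 result is in principle withheld. The treatment is blinded. SAP 3.2.2 does allow the code to be opened when it is needed to decide further treatment. Protocol 6.6.1 and 9.3 confine this to emergencies, and SAP 4.5 rates premature unblinding as a major deviation. The route exists but is narrow.

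**4. What the documents say about recovery.** Protocol 2.3 reports 18 healthy subjects given one 0.5 IU/kg infusion, with a median baseline of 235 mg/dL. Protocol 2.4.1 says bleeding risk appears increased when fibrinogen stays below 40 mg/dL for longer periods.

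| Time from start of infusion | Median (mg/dL) | Share of 235 | Multiple of 40 |
|---|---|---|---|
| 24 h | 117 | 117/235 = 49.8% | 117/40 = 2.9 |
| 48 h | 147 | 147/235 = 62.6% | 147/40 = 3.7 |
| 72 h | 163 | 163/235 = 69.4% | 163/40 = 4.1 |

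Fibrinogen is still reduced at 1 to 3 days, yet well above 40 mg/dL. This is a different regimen from an infusion followed by three injections, so it does not establish Day 8 levels or bleeding risk in either direction. Protocol 9.3 says levels normalise within a few days of stopping. Protocol 2.4.2 puts viscosity near its pretreatment value about 10 days after treatment ends.

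**5. Overlap of the two sections.** 90 − 8 = 82 days. With visit windows it is 83 − 9 = 74 to 97 − 7 = 90 days. This is how long both texts apply to a patient.

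**6. Effect on the analyses.** The 7.3 permission depends on the Day 8 measurements, so treatment given under it follows the Day 8 audiogram and cannot change the primary variable. SAP 9 treats all secondary variables, including Day 30 and Day 90, as exploratory.

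**The case against.** The best defence is that the protocol already contains the rule. A ban that names drugs and states a single exception is hard to displace with one general sentence, and the five-class list appears in four other places. The heading of 7.3 suggests that the sponsor had post-study care in mind. No passage calls pentoxifylline, naftidrofuryl or hydroxyethyl starch standard of care, and Protocol 2.1 describes all current treatments as empiric. For harm to arise, an investigator would have to regard these drugs as standard care and also override a ban that names two of them as antiplatelet drugs. Section 6.4.1 also sets specific intervals after the start of study drug, 5 days for thrombolytics and 72 hours for anticoagulants, and both end before Day 8.

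Most of this stands. The specific ban is the more natural governing text, and reading the barred drugs into standard care is an inference. But the heading does not cure a sentence whose only time point is Day 8, and no precedence is stated. The intervals do not shorten the ban either: both classes also appear on the study-long list, and no interval is given for antiplatelet drugs.

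**Conclusion.** Section 7.3 is wrong as written. It is a minor internal contradiction with a safety aspect: the exposed situation is an antiplatelet drug started 1 to 3 days after the last dose, by a blinded investigator without a current fibrinogen value. This assumes that dosing was completed and that the investigator follows 7.3 literally. The documents give no rate of use of barred drugs after Day 8, so the number of patients affected and any added bleeding risk cannot be estimated.

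A reader might infer more, and the documents do not support it:
- *That the plan authorises the barred drugs or has no rule.* The rule is there; 7.3 is out of line with it.
- *That patients face 82 days of bleeding hazard.* That figure measures textual overlap. Protocol 9.3 and 2.4.2 point to a recovery of days.
- *That the efficacy result is compromised.* The Day 8 primary analysis is unaffected, and the later results are exploratory.
- *That drugs named in 6.4.1 cannot serve as rescue vasodilators.* Section 6.5 leaves vasodilators undefined and 6.4.1 exempts rescue medication, so the question is open.

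**What to change.** Replace the sentence in 7.3 with:

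> A patient who has not improved, or has worsened, by the Day 8 visit may receive the rescue medications listed in Section 6.5; the prohibitions in Section 6.4.1 otherwise remain in force until Day 90. After the Day 90 visit the patient may receive accepted Standard of Care.

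The word *otherwise* is needed because 6.4.1 also lists systemic corticosteroids, which 6.5 allows. The last sentence keeps the post-study provision that the heading announces.

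Under Protocol 13.2 the change needs sponsor, ethics committee and authority approval. Until then, a site letter may only remind sites that the existing 6.4.1 ban and 6.5 list apply to Day 90. It should not introduce new restrictions. Separately, ask the sponsor to decide whether drugs named in 6.4.1 may be given as vasodilators under 6.5.

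The cost is small. No new data are needed, and non-improvers keep every option in 6.5. SAP 2 expects only a few more evaluable patients than the 30 planned for the interim analysis, so the amendment would reach few people and the letter does most of the work. An investigator who considers a barred drug necessary can withdraw the patient under Protocol 5.1.4, which may cost Day 30 or Day 90 data.
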